### Variables

#### Main variables

The primary outcomes will be the changes from the baseline of the VAS and the Western Ontario and McMaster Universities Osteoarthritis Index (WOMAC) for pain at the completion of treatment at 12 weeks.

#### Secondary variables

Secondary variables to be considered are the following: the change in the secondary efficacy variables from the baseline of the Short Form 36 version 2 health survey (SF-36v2) (patient-perceived quality of life), the change in plasma cortisol and beta-endorphin levels, the scores for the Goldberg Anxiety and Depression Scale (GADS), changes in pain medication use, changes in functional capacity and stiffness (WOMAC subscales), and VAS scores measured at 1 month, 3 months, 6 months, and 1 year after study commencement.

### Procedure

Figure 1 describes the trial protocol. The eligibility of prospective participants will be determined by a researcher who is not involved in the assessment or treatment of the participants. Ethical approval was obtained from the Balearic Islands Human Research Ethics Committee in July 2013 (CEI-IB, #IB 2077/13 PI).

Upon arrival at the Clinic for Pain Treatment, recruited patients will be informed once again about the trial objectives, and any questions or doubts that the patient might still have with respect to the study will be resolved. Patients will then be informed that they are testing a new EA technique for knee pain treatment. Placebo or sham acupuncture (SA) will not be mentioned to the patient during the interview or referred to in the informed consent form. Subjects will be placed into one of two study groups (with a strict 50 % probability), and to reinforce and encourage treatment follow-up, patients will be told that the effects are to be perceived over the medium- to long-term time frame. Patients will be re-assessed to ensure that they still comply with the selection criteria and that they have not acquired any new criteria for exclusion. Participants will provide informed consent in the first baseline visit (Table 1).

**Table 1 Tab1:** Planned visit schedule for treatment and follow-up, indicating visit number and frequency

	Visits									
	0	1st	2nd -7th	8th	9th	10th	11th	12th	13th-14th	15th
			(2 weekly /month)	(follow-up 1st month)	(2nd month)	(follow-up 3rd month)	(every 45 days)	(follow-up 6th month)	(every 2 months)	End of follow-up (1 year)
**Patients**										
Patient’s evaluation and collection of the relevant data	√									
Inclusion/Exclusion criteria	√									
Explanation of the objectives of the procedure and how it works	√									
Informed consent	√									
Randomization and blinding		√								
Expectation of acupuncture				√		√		√		√
**Treatment**										
Electro-acupuncture (EA)		√	√	√	√	√	√	√	√	√
Sham acupuncture (SA)		√	√	√	√	√	√	√	√	√
**Outcomes**										
Visual analogue scale (VAS)	√			√		√		√		√
McMaster Universities Osteoarthritis Index (WOMAC)	√			√		√		√		√
Medication use	√			√		√		√		√
Goldberg Anxiety and Depression Scale	√			√		√		√		√
Short Form Health Survey (SF-36v2)	√			√		√		√		√
Blood sample collection	√			√		√		√		√
**Trial evaluation**										
Adverse event				√		√		√		√
Outcome assessment										√
Reasons of drop-outs or withdrawals				√		√		√		√
Satisfaction and expectations Survey										√

### Baseline visit

The researcher will re-collect clinical data of patients, including age, sex, and body mass index. In the baseline interview, the participants will not yet be assigned to a treatment group.*Pain perception assessment* will be based on (1) the VAS score and (2) the WOMAC scale pain score. The VAS is a continuous scale made up of a 10-cm, unmarked, horizontal line, upon which the subject makes a hash mark depending on the amount of pain felt; a mark on the far left of the line indicates “no pain” (score of 0), and a mark to the far right qualifies as “pain as bad as it could be” or “unbearable pain” (score of 100). The WOMAC scale is used to evaluate the condition of patients with OA of the knee and the hip and includes pain, stiffness, and physical functioning of the joints. This scale measures five items for pain (with a score range of 0–20), two for stiffness (score range of 0–8), and 17 for functional limitation (score range of 0–68). The physical functioning questions cover everyday activities. These scales will be used separately and will not be summed. Patients will respond orally to the five levels with the following criteria: “none” = 0, “a bit” = 1, “quite a bit” = 2, “a lot” = 3, and “very much” = 4. If two or more questions are left unanswered, the scale will be declared invalid. If the patient does not respond to one question, a mean will be taken from the results of the other questions. The range will be 0–98.*Analgesic medicine use*. This questionnaire will have four questions developed according the EUROHIS (European Health Interview Survey) recommendations in order to harmonize the information regarding medicine use [31]. Subjects will be asked (1) about the prescription medicine their general practitioner may have prescribed for them (“Have you taken any pain medicine prescribed by your general practitioner?”) as well as any medication not prescribed by their general practitioner (“Have you taken any pain medicine not prescribed by your general practitioner”) and (2) whether or not their prescribed and non-prescribed pain medication use has increased or decreased.*The degree of functionality and stiffness* according to the WOMAC scale. There are two questions for stiffness (scale of 0–8) and 17 questions for functional limitation (score range of 0–68). Each question will be answered orally with the following criteria: “none” = 0, “a bit” = 1, “quite a bit” = 2, “a lot” = 3, and “very much” = 4. If two or more questions are unanswered, the scale scores will be declared invalid and not counted.*Anxiety/depression level* according to the GADS. This consists of two subscales (of nine questions for each scale): an anxiety scale (1–9) and a depression scale (10–18). The first questions for each scale (1–4 and 10–13) are preconditioned questions to determine whether the patient should attempt to answer the rest of the questions of the two subscales. Effectively, at least two questions must be answered affirmatively in the first scale (1–4) for the patient to continue; in the second scale, one answer is sufficient for questions 10–13 for the patient to continue with the rest of the questions. This study will use the Spanish version validated by Montón et al. [32].*Degree of quality of life*. This will be assessed according to the SF-36v2 questionnaire and is compounded by 36 items, which yield an 8-scale profile of functional health and well-being scores as well as psychometrically based physical and mental health summary measures and a preference-based health utility index. The Spanish version of the SF-36 questionnaire by Ware and Sherbourne [33] has been correctly translated and standardized and has been given the Spanish title of *Cuestionario de Salud* SF-36 [34].

The first baseline plasmatic sample will be extracted from the antecubital vein to evaluate beta-endorphin and cortisol levels, and the sampling time will be between 9 and 14 h. To avoid any diurnal variation in plasmatic hormonal levels, subjects will always be assigned the same hour for the extractions. Five blood samples (5 ml each) from each patient will be taken under aseptic conditions from the antecubital vein; one extraction will required before the treatment, one at 1 month after the start of treatment, one at 3 months, one at 6 months, and one at the end of treatment. Except for the first pre-treatment sample, extractions will take place 5 min after finishing the acupuncture treatment. Once extracted, blood will be placed in a refrigerated tube with EDTA (ethylenediaminetetraacetic acid) anticoagulant and centrifuged immediately. Plasma will be extracted with a micropipette and divided in two equal fractions (one for the cortisol and one for the beta-endorphin analysis). Samples will be stored at −70 °C until the analysis. The baseline interview treatment will have no assigned sampling time and will occur on the first day, when the subject is assigned to his or her respective treatment group.

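### The WOMAC missing-answer rule does not say whether blanks are counted per subscale or over the whole form, and its flat cutoff of two is strict for the 17-item function score

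*Protocol article*

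**What the plan says.** The Baseline visit section of the protocol article describes the WOMAC as five pain items (0–20), two stiffness items (0–8) and 17 function items (0–68), each scored 0 to 4 and answered orally. On the use of the scores it says "These scales will be used separately and will not be summed".

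Two scoring rules follow in the text on pain. The first is "If two or more questions are left unanswered, the scale will be declared invalid". The second says that a single unanswered question is handled with a mean of the remaining ones. Then comes "The range will be 0–98".

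The text on functionality and stiffness, later in the section, repeats the two-blank rule; there "the scale scores will be declared invalid and not counted". It does not repeat the one-blank provision.

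Main variables names WOMAC pain as a primary outcome alongside the VAS. Secondary variables lists functional capacity and stiffness as WOMAC subscales. No WOMAC total is an outcome.

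**The concern.** The rule discards data, so its unit matters, and the unit is not given. The section uses the word scale both for the whole instrument (the WOMAC scale, with its three domains) and for the parts that are kept separate. A scorer who takes the rule together with the total range that follows it could count blanks over 24 items. On that reading, a patient who answers all five pain questions but leaves two function questions blank loses a primary outcome value.

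On the other reading, the same absolute count of two is applied to subscales of 5, 2 and 17 items. It tolerates one blank in five for pain but only one in 17 for function. A function score with 15 of 17 answers would be thrown away.

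If the unit is left open, the choice between the readings may be made when the data are scored. It would then decide which patients have a WOMAC pain value for the primary comparison.

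**Working it through.** **Range.** Inputs are the item counts and the 0–4 scoring in the Baseline visit section.

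- Pain: 5 × 4 = 20
- Stiffness: 2 × 4 = 8
- Function: 17 × 4 = 68
- Total: 20 + 8 + 68 = 96

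The three subscale ranges reproduce. The stated maximum of 98 does not: 98 / 4 = 24.5, which is not a whole number of items, and no combination of the subscales gives 98.

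**How often each reading voids a score.** The article gives no item non-response rate. I assume a rate q that is the same for every item and independent between items, and show a range.

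P(at least 2 blank of n) = 1 − (1 − q)^n − n·q·(1 − q)^(n−1)

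The chance that all five pain answers are present and the form is still void is (1 − q)^5 × P(at least 2 blank of the other 19). The 19 are the stiffness and function items together. Worked at q = 2%: 0.9039 × 0.0546 = 0.0494, or 4.9%.

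| Assumed q | Whole form void (n = 24) | Form void with all 5 pain answers present | Pain void, per subscale (n = 5) | Function void, per subscale (n = 17) |
|---|---|---|---|---|
| 0.5% | 0.6% | 0.4% | 0.02% | 0.3% |
| 1% | 2.4% | 1.5% | 0.1% | 1.2% |
| 2% | 8.3% | 4.9% | 0.4% | 4.5% |
| 3% | 16.1% | 9.4% | 0.8% | 9.1% |

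The two readings therefore differ about twentyfold or more in lost pain scores (at 2%, 8.3% against 0.4%).

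**Effect of a proportional function rule.** If function is scored whenever at least 14 of 17 items are answered, it is void only with 4 or more blanks. P(at least 4 blank of 17) is 0.002, 0.03 and 0.14% at q = 1, 2 and 3%, against 1.2, 4.5 and 9.1% under the cutoff of two.

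**Pain under the per-subscale reading.** One blank is filled with a mean and two blanks void the score. For five items this already means that four answers are enough.

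**Stiffness.** With two items, a cutoff of two voids the score only when both are blank. Whether one blank may be filled is not stated, because the text on functionality and stiffness omits that provision.

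**The case against.** The strongest reply is that the per-subscale reading is the more natural one. The sentence keeping the scales separate comes shortly before the rule, and the scales it means are the three subscales. The rule is stated a second time for function and stiffness, which a single 24-item rule would not need, and there it speaks of scores in the plural. Filling a blank pain answer with a mean taken mostly over function items would also sit badly with subscales that are kept apart. All of this stands. A reader might infer that the plan does void complete pain scores because of blanks elsewhere. The article does not say so; that follows only on the less natural reading.

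A reader might also tie the wrong maximum to the loss of data. It causes none: no total is an outcome, so 0–98 affects no planned analysis. Its only relevance here is that a total range, printed just after the rule, leaves the whole-form reading open.

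The non-response rates are assumptions. Answers are given orally to interviewers, who can notice a skipped question, so rates of 0.5% or less are plausible and the effect would then be small. It may seem likely that blanks come from sicker patients who cannot do an activity, but the article offers nothing on this, and the independence assumed above would then fail.

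Finally, a strict cutoff for function is a stated choice for a secondary variable, and the article prescribes no particular proportion. That is fair, but the choice costs function data under either reading. A uniform 80% threshold would not be a safe replacement: on a two-item scale it would require both answers and could discard stiffness scores that the present rule keeps.

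**Conclusion.** The point holds as a gap in a scoring rule that the article itself fixes, not as a shown loss of primary data. The unit of the two-blank rule is undefined. The size of the consequence for WOMAC pain depends on the reading: between about 0.4% (q = 0.5%) and 9.4% (q = 3%) of forms voided with complete pain answers if blanks are counted over the form, and under 1% of pain scores voided if they are counted per subscale. On the more natural reading the remaining cost falls on function, with about 1.2 to 9.1% of scores voided at assumed rates of 1 to 3%. All these figures rest on equal and independent item non-response, which the article neither gives nor supports. The range of 0–98 is an arithmetic slip in a total that is not used. The change is worth making because it is cheap and settles in advance who has a valid pain score.

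**What to change.** - State that the two-blank and one-blank rules apply within each subscale, and that blanks in one subscale never void another. Pain is then never lost because of stiffness or function answers.
- Pain: keep the present rule (four of five answered is enough), with the mean taken over the pain items only.
- Function: replace the cutoff of two by prorating from the answered function items when at least 14 of 17 are present.
- Stiffness: state that the one-blank mean applies here too, so that the score is void only if both items are blank.
- Delete the total range. If a total is kept for description, it runs 0–96.

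The cost is a few sentences and the scoring syntax, best settled before unblinding. The small downside is a few more prorated function scores: at an assumed 2%, about 4.5 − 0.03 = 4.4% of function scores (from unrounded values) would be prorated over two or three blanks instead of discarded.

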**Methods/design:**

This study is a placebo-controlled, randomized, double-blind, parallel design trial. One hundred sixty out-patients who are more than 50 years old and who have osteoarthritis of the knee will be recruited from the island of Mallorca, Spain. Each participant will be randomly placed into one of two groups: (sham) electro-acupuncture non-insertion technique and real electro-acupuncture.

Acupuncture treatments will be the Traditional Chinese Medicine type. The patients will be evaluated after a period of 1 month (with two weekly sessions), 3 months (with one monthly session), 6 months (with one session every 45 days), and 1 year later with follow-up sessions at the end of the study (with one session every 2 months).

The primary outcomes will be based on the observed changes from the baseline of the visual analogue scale (VAS) and the Western Ontario and McMaster Universities Osteoarthritis Index (WOMAC) for pain measured at 12 weeks after the end of treatment.

Also to be included in the study are the possible changes in the secondary efficacy variables from baseline as assessed by the Short Form 36 version 2 health survey (patient-perceived quality of life), patient plasma cortisol and beta-endorphin levels at the different treatment stages, the Goldberg Anxiety and Depression Scale, pain medication use, functional capacity and stiffness (WOMAC subscales), and a VAS. These variables will be assessed at 1 month, 3 months, 6 months, and 1 year after study commencement.

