Although cortisol release is one of the consequences of HPA system activation, some studies have shown responses opposite to the cortisol release produced by acupuncture practice. Normal individuals show opposite cortisol responses to those with chronic pain conditions. This suggests that if the HPA axis contributes to the efficacy of acupuncture, its role is more complex than simply deactivating this system. Rather the contribution may depend on the population being studied. One of the objectives of this study is to provide more data to elucidate possible mechanisms of action and to show correlations between reductions in pain and changes in hormonal markers of HPA axis function. This will aid in establishing whether changes in HPA axis are causal or merely epiphenomenal in treatment efficacy.

This following study is a project to assess the effectiveness of EA for the treatment of common pathologies that involve chronic OA pain in knee. Additionally, it will evaluate pain perception, plasma endorphin and cortisol levels, patient quality of life, and the need for pharmacological drugs regardless of whether EA is applied.

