### Next several visits for treatment (two sessions per week until the completion of eight sessions)

The same treatment will be repeated according to group. In the last session, blood samples will be drawn 5 min after the treatment completion, at the same time of day as the previous extraction.

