### At 1 month’s time

The interviewers will repeat the assessments for pain level, analgesic consumption, and the type of treatment that the patient believes he or she is receiving as well as the assessment by the WOMAC scale and the GADS. The patient will once again answer the quality-of-life questionnaire (SF-36v2). Once the forms have been completed, treatment will be administered to the patient.

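### Hormone change from baseline compares a pre-treatment sample with samples drawn 5 minutes after a session, so acute response and lasting change cannot be told apart

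*Protocol article*

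**What the plan says.** The Baseline visit section plans five blood samples per patient: "one extraction will required before the treatment, one at 1 month after the start of treatment, one at 3 months, one at 6 months", and a last one at the end of treatment. On their relation to the session it says "Except for the first pre-treatment sample, extractions will take place 5 min after finishing the acupuncture treatment". The section on the next treatment visits repeats this for the eighth session: "In the last session, blood samples will be drawn 5 min after the treatment completion, at the same time of day as the previous extraction".

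Table 1 agrees. Blood is taken at visit 0, where there is no treatment, and at the 8th, 10th, 12th and 15th visits, each of which includes a session. Randomization is at the 1st visit, after the baseline sample.

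The Secondary variables section lists "the change in plasma cortisol and beta-endorphin levels", and the abstract gives the reference point: "possible changes in the secondary efficacy variables from baseline". The Background states the use to be made of the result: "to show correlations between reductions in pain and changes in hormonal markers of HPA axis function", in order to help decide whether the hormonal changes drive the benefit or only accompany it.

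For the order of events within a visit, the section on the 1-month visit says of the questionnaires: "Once the forms have been completed, treatment will be administered to the patient".

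**The concern.** A change score is easiest to interpret when both of its values are taken under the same conditions. Here the first value precedes any treatment, and each later value follows 20–30 minutes of a session by 5 minutes. In the EA arm that session includes electrical stimulation at the highest intensity the patient tolerates. In the sham arm no current is applied.

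If EA raises or lowers either hormone briefly, that response appears in every follow-up value. It would be reported as change at 1, 3, 6 and 12 months even if levels returned to baseline between sessions. The reverse is also possible: an acute response of opposite sign could hide a lasting difference. The Background itself notes that studies have found cortisol moving in opposite directions after acupuncture.

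At stake is the mechanistic conclusion about the HPA axis and the opioid system, in particular the intended reading of the correlation with pain relief.

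**Working it through.** **1. What the samples can identify.** For each arm, let L be the lasting change since baseline and A the acute response to that day's session. The mean observed change is

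- EA: L_E + A_E
- Sham: L_S + A_S
- Difference between arms: (L_E − L_S) + (A_E − A_S)

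With one post-session draw per visit there is one observed mean per arm and visit, and two unknowns. No analysis of these samples separates L from A. The rule that each patient is sampled at the same hour controls diurnal variation, not the session.

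**2. What cancels.** The Control group section gives sham patients the same sessions and schedule as EA patients. Any part of A common to both arms (handling, expectation, venipuncture) drops out of the difference. What remains is A_E − A_S, the EA-specific acute response. Because the baseline sample precedes randomization, the expected difference in change equals the expected difference in post-session level, which is a valid randomized contrast. Within-arm changes keep the whole of A.

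**3. The pain-hormone pairing.** At 1 month the forms are completed before the session and blood is drawn 5 minutes after it. The correlation therefore pairs a pre-session pain score with a post-session hormone level. The Subsequent visits section gives no order for 3, 6 and 12 months, so the mismatch is documented for 1 month only.

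**4. Number of evaluable patients for an illustration.** The Participants section gives a difference of 3, SD 4, two-sided alpha 0.01, power 0.95 and 20% attrition:

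- n per group = 2 × (2.576 + 1.645)² × (4/3)² = 63.3, rounded up to 64
- with attrition, 64 / 0.80 = 80 per group, 160 in total

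This reproduces the stated sample size. It concerns VAS pain and supplies only the 64 per arm used next.

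**5. Illustration of size.** The documents give no hormone means, SDs or acute effects. Assume two-sided alpha 0.05, and express the between-arm differences L and A in SD units of change. The noncentrality parameter is (L + A) × √(64/2) = 5.657 × (L + A), with 126 degrees of freedom.

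| Lasting difference L | Acute difference A | Chance of a significant difference in change |
|---|---|---|
| 0 | 0 | 5% |
| 0 | 0.25 | 29% |
| 0 | 0.5 | 80% |
| 0 | 0.75 | 99% |
| 0.5 | 0 | 80% |
| 0.5 | −0.5 | 5% |

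The third and fifth rows are identical: a purely acute and a purely lasting difference of the same size give the same result. These are valid rejections for post-session level. They mislead only if they are read as lasting change.

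**The case against.** The strongest reply is that the plan measures something well defined. Both arms are sampled 5 minutes after their own session throughout, so time since stimulation is constant. No outcome definition calls the hormone change resting or sustained, and the Background partly frames the HPA question as cortisol release in response to acupuncture, which a post-session sample addresses directly. A pre-session draw would have its own difficulty: the previous session would be days earlier at 1 month and about 2 months earlier at 12 months. The correlation is stated as an aim, and its analysis may be set out in a fuller plan.

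Much of this stands. It defends the between-arm comparison of post-session levels. It does not defend a within-arm change from a pre-treatment baseline, or a causal reading of that change's correlation with pain. No later analysis plan can supply samples that were not drawn.

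A reader might infer more than the documents support:

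- **That the mechanistic aim cannot be answered at all.** It can be answered for post-session levels, but not for lasting change.
- **That the baseline sample is taken at rest.** The text says only that it precedes treatment and sets no rest condition.
- **That the same-hour rule is contradicted by** "The baseline interview treatment will have no assigned sampling time". That sentence is garbled. The same section gives a 9 to 14 h window for the baseline sample and a same-hour rule, and the sentence may mean only that no blood is drawn at the first treatment session.
- **That four of five samples being post-session measures the bias.** It is a count of samples and says nothing about the size of the acute response.

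**Conclusion.** The point holds in a limited form. Every follow-up sample is post-session and the only baseline sample is pre-treatment. Within-arm hormone change, and any EA-specific part of the between-arm difference, therefore mixes acute response with lasting change in proportions that the planned data cannot reveal. EA versus sham remains valid as a comparison of post-session levels. At 1 month, the planned correlation also pairs measurements from opposite sides of the session.

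The size of the mixing is unknown. The figures of 29%, 80% and 99% rest on assumed acute differences of 0.25, 0.5 and 0.75 SD, 64 evaluable patients per arm and two-sided alpha 0.05, and show only what could happen. The point affects secondary mechanistic outcomes. The primary VAS and WOMAC pain outcomes and the sample size of 160 do not depend on it.

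**What to change.** Define the secondary outcome as the post-session cortisol and beta-endorphin level at each follow-up, compared between arms with the baseline value as covariate. State in the Background and under Secondary variables that within-arm change and the pain-hormone correlation will not be interpreted as lasting or causal change in the HPA axis or the opioid system. This needs no extra sample and keeps blood already drawn usable. The cost is a narrower mechanistic claim and a covariate-adjusted model for these outcomes.

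If lasting change is the intended target, wording alone is not enough: the follow-up draw would have to precede the session, at the same clock hour as baseline. The acute response would then be lost, time since the last session would differ between visits, and samples already taken in this recruiting trial would not be comparable.

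In either case, clarify the sentence on the baseline interview and sampling time rather than delete it, since it may be the text's way of saying that no blood is drawn at the first treatment session.
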